## Abstract

**Background:**

Women in pregnancy and postpartum have an increased vulnerability to develop an affective disorder. Affective disorders in pregnancy are associated with an increased risk of prematurity, dysmaturity (foetal weight below the 10^th^ percentile as determined by ultrasound) and the development of postpartum depressive disorder. Untreated affective disorders and their complications may also result in considerable costs. Recent meta-analyses showed that interventions during pregnancy are less effective than postpartum interventions probably because of high attrition due to the barriers pregnant women experience with attending sessions outside their homes. An internet-based self-help intervention may overcome these barriers as it can be followed at home, and also in one’s own time. Such internet interventions showed to be effective for decreasing affective symptoms in general.

This randomised clinical trial examines whether an internet-based self-help intervention is effective in the reduction of affective symptoms in pregnancy and postpartum and results in an improvement of the perinatal outcome. We will also determine the cost-effectiveness of the intervention.

**Methods/design:**

We will investigate the effectiveness of a 6 week internet-based self-help problem solving treatment (PST) for affective symptoms in pregnancy. We aim to include 286 women with mild to severe affective symptoms who will be randomly assigned to the internet-based intervention or a waiting list control group. Primary outcome measures are affective symptoms and the perinatal outcome. Secondary outcome measures are quality of life, and economic costs. All assessments are based on self-report and will take place at baseline (T0), 10 weeks later (after completion of the intervention (T1), 4 weeks before the expected day of birth (T2), and 6 weeks after delivery (T3). The control group will be measured at the same moments in time. Analysis will be based on the intention-to-treat principle.

**Discussion:**

If shown (cost) effective, internet-based PST will offer new possibilities to treat pregnant women for affective symptoms, to improve their perinatal outcome and to prevent the development of postpartum depressive disorders.

**Trial registration:**

Nederlands Trial Register:
NTR4321

## Background

Women in pregnancy and postpartum have an increased vulnerability to develop a depression or anxiety disorder, both affective disorders. The prevalence of depressive and anxiety disorders during pregnancy is 12 and 11% respectively
[1]. The prevalence rate of mild affective symptoms is estimated to be 17%
[2]. Depressive and/or anxiety symptoms in pregnancy are often not diagnosed because of overlapping symptomatology with pregnancy itself. They remain therefore often not recognised
[3, 4].

Affective disorders are associated with adverse perinatal outcomes such as an increased risk of prematurity, dysmaturity, and decreased breastfeeding initiation
[3, 5]. Moreover, antenatal depressive and/or anxiety symptoms are a risk factor for the development of postpartum depressive disorder and therefore for impaired development of the child
[6–11]. Therefore, untreated affective disorders and their complications may result in considerable costs
[8]. Consequently, prevention of the occurrence of an affective disorder during pregnancy is important for mother, child and society at large.

A recent meta-analysis, which included 28 Randomised Controlled Trials (RCT’s), showed that pre- and postpartum psychological interventions reduced the number of women who developed postpartum depression
[9]. The most effective interventions were postpartum (instead of antenatal) individual interventions (instead of group interventions) aimed at women with multiple risk factors (instead of offering it to all women). Attrition was noted as one of the main problems to accomplish a sufficient intervention dose. This is probably due to the fact that pregnant women have many specific barriers to attend sessions outside their home. The following interventions appear to show promise in the reduction of antenatal depressive symptoms and the subsequent prevention of postpartum depressive disorder: lay telephone support, home visits by nurses, and interpersonal therapy (IPT).

An internet-based self-help intervention may overcome pregnancy specific barriers related to face-to-face interventions. Internet interventions are easy accessible, home-based and can be followed in one’s own time. There is no waiting list and there is also a reduction in therapist time and costs. This type of intervention is therefore a promising approach in the treatment of depressive and anxiety symptoms in pregnant women.

In recent years self-help internet programs have become increasingly popular in mental health care. They are based on evidence based psychological treatments. Nowadays, numerous randomised controlled trials are available demonstrating the effectiveness of internet-based self-help interventions for different mental disorders such as depression
[12, 13], anxiety
[14, 15], alcohol
[16], and insomnia
[17]. Various treatment modalities have been applied within these trials, for example Cognitive Behavioural Therapy (CBT) and Problem-Solving Therapy (PST). It has been demonstrated that internet self-help treatments provided with support are more effective than those without any support
[18]. To our best knowledge no evidence is available on self-help internet interventions for depressive and anxiety symptoms in pregnancy.

We will examine the effectiveness of an intervention based on an existing, evidence based internet self help version of PST
[19] compared to a waiting list control condition on (1) the reduction of depressive and anxiety symptoms post intervention, end of pregnancy and 6 weeks postpartum and, (2) the improvement in perinatal outcomes (for example pre-term birth, growth restriction and breastfeeding initiation). We will also (3) determine cost-effectiveness using a societal perspective. We will further explain the intervention in the method section.

## Methods and design

### Study design

The study is a randomized controlled trial with an active intervention arm and a waiting list control condition. The intervention is based on problem solving treatment and will be offered through the internet. It will be guided by a trained coach. Participants in the control condition are offered access to the same intervention after the last follow-up of the trial (6 weeks postpartum). Both groups are allowed to use concurrent treatment (care-as-usual) as well. This additional care will be monitored.The study protocol, information brochure and informed consent were approved by the Medical Ethics Committee of the VU University Medical Center (registration number 2013.275). Figure 
1 displays the flowchart of the study design.

**Figure 1 Fig1:**
[figure not shown]
**Flowchart selection, inclusion, intervention and measurement.**

### Inclusion and exclusion criteria

We will include participants who are at risk for developing postpartum depression. More specifically, we will include participants of 18 years and older, who are pregnant but are at least 10 weeks before the expected delivery date, and have at least mild symptoms of depression or anxiety. Symptoms of depression are measured with the Center for Epidemiological Studies Depression scale (CES-D) and symptoms of anxiety with the Hospital Anxiety and Depression Scale- Anxiety subscale (HADS-A)
[20, 21]. Patients are eligible if they score at least 16 on the CESD and/or 8 on the HADS-A. Participants who indicate that they either intend to harm themselves or want to attempt suicide (as assessed by one question of the Web Screening Questionnaire (WSQ)
[22]) will be excluded. They are advised to consult their general practitioner to obtain more tailored care. Receiving psychiatric treatment including psychotherapy or the use of psychopharmacological agents such as antidepressants is allowed. Any additional treatments will be monitored through patients self-report at the end of study.

### Recruitment

Participants will be recruited from the general Dutch population by means of banners on internet websites and advertisements in newspapers and magazines for pregnant women. These banners and advertisements refer to our study website. The website provides general information about the study and women can register online. All registered women will then be informed in more detail. They will also receive an informed consent form and a link to a baseline questionnaire. Only women who return a signed informed consent, complete the online baseline questionnaire, meet inclusion criteria and do not meet exclusion criteria will be included and randomized. Participants with very severe depressive or anxiety symptoms (CESD ≥ 25 or HADS-A ≥ 12) will be advised to contact their general practitioner as well, since the possibility exists that they need additional treatment. They will not be excluded since there exists evidence that the intervention is also helpful in case of severe depressive symptoms
[23, 24].

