### Suicidality

We will use one question of the WSQ
[28] to asses suicidality. We will contact participants with a score 3 by telephone to give them advice about obtaining additional treatment. If needed we will also contact their general practitioner. For that reason we will also ask the telephone number of the participant and the name of het general practitioner.

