### Assessments

All assessments are based on self-report and will take place online (Table 
1). We will measure at baseline (T0), 10 weeks later (although it is possible to finish the intervention in 6 weeks we know that there will be some people who need more time. To ensure that the post-test assessment takes place after completing the intervention we will perform the post-test assessments after 10 weeks.), when the intervention group has finished the intervention (T1), 4 weeks before the expected day of birth (in order to registrate symptoms of relapse (T2), and 6 weeks after delivery (T3). Participants starting the intervention after 24 weeks of pregnancy will not be assessed at T2, since the time period between T1 and T2 will be too small.

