**Table 1 Tab1:** **Assessment time table**

	T0	T1	T2	T3
CES-D	X	X	X	X
HADS	X	X	X	X
WSQ	X			X
EPDS	X	X	X	X
TiC-P	X	X	X	X
Euroqol	X	X	X	X
Demographic variables	X			
Delivery outcome				X

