### Sample size and statistical analysis

Analyses will be conducted according to intention-to-treat as well as per protocol principle. To study differences between the conditions we will use linear mixed models with symptoms of depression and anxiety as dependent variables, time indicators and treatment dummy as predictors, since these types of models account for drop out over time. We will compute both within group effect sizes and between group effect sizes. The within group effect sizes are standardized differences of (predicted) means of the follow up scores and baseline scores. The between group effect sizes concern differences between within group effect sizes. We assume that the between group effect size (Cohen’s d) at the end of the study will be at least 0.40, because this has been demonstrated in a meta-analysis on supported internet treatments in general
[13] and in previous studies using the same problem solving internet treatment
[19, 25]. Using an alpha of 0.05 (two-tailed), a statistical power (1-bèta) of 0.80, and an attrition rate of 30%
[19] we need 143 respondents in each arm. All analyses will be conducted using SPSS for Windows, version 20 and STATA 10.0.

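### As described, the advice to see the general practitioner at CES-D ≥ 25 or HADS-A ≥ 12 is given only at entry, and no score triggers advice at T1 or T2

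*Protocol article*

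**What the plan says.** The protocol article ties a score to an action in three places.

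- **Inclusion and exclusion criteria.** Women who report an intention to harm themselves or attempt suicide on one WSQ question are excluded. "They are advised to consult their general practitioner to obtain more tailored care".
- **Recruitment.** "Participants with very severe depressive or anxiety symptoms (CESD ≥ 25 or HADS-A ≥ 12) will be advised to contact their general practitioner". The reason given is "since the possibility exists that they need additional treatment". The next sentence explains why these women are nevertheless included.
- **Suicidality.** On the WSQ item, "We will contact participants with a score 3 by telephone to give them advice about obtaining additional treatment", with contact to the general practitioner if needed. No visit is named.

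Table 1 ("Assessment time table") schedules CES-D, HADS and EPDS at T0, T1, T2 and T3, but the WSQ at T0 and T3 only. Under Assessments, the purpose of the second follow-up is given as "in order to registrate symptoms of relapse (T2". The timing of T1 is explained as follows: "To ensure that the post-test assessment takes place after completing the intervention we will perform the post-test assessments after 10 weeks". Women who start after 24 weeks of pregnancy have no T2.

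**The concern.** The reason for the advice is that a woman scoring this high may need more treatment than the trial gives her. That reason applies equally when the same score is recorded at T1, T2 or T3. Eligibility starts at CES-D 16 or HADS-A 8. A woman can therefore enter with, say, CES-D 16 to 24 and HADS-A below 12, receive no advice, worsen, and record a score above the cut-off at a later online assessment without any described response. T2 is there to detect relapse, yet no response to relapse is described.

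By T1 the six-week course should be finished, and controls are not offered it until six weeks postpartum, so the gap is the same in both arms. What is at stake is the safety of symptomatic pregnant women assessed wholly online.

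**Working it through.** **Step 1. Set the rules against the schedule.** The table shows which described action can operate at each assessment.

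| Action | T0 | T1 | T2 | T3 |
|---|---|---|---|---|
| WSQ suicidality: exclusion with advice | yes | – | – | – |
| CES-D ≥ 25 or HADS-A ≥ 12: advice to contact the general practitioner | yes | – | – | – |
| WSQ score 3: telephone call | yes | no WSQ | no WSQ | yes |
| CES-D and HADS collected | yes | yes | yes | yes |

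The entries rest on different kinds of evidence. The empty WSQ cells at T1 and T2 are stated outright in Table 1, so the telephone rule cannot operate there. The entry-only reading of the severity advice is an inference from its place under Recruitment and from the sentences around it. The weekly coach e-mail (Intervention section) is no substitute: it concerns assignments, reaches only the intervention arm and is not triggered by a score.

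**Step 2. Who is affected.** The gap concerns women below both cut-offs at entry who first cross one later. Women above a cut-off at entry have already been advised. For women starting after 24 weeks, the affected follow-ups are T1 and T3. The article gives no score distribution, so no count or percentage can be stated.

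**Step 3. What the remedy could do to the contrast.** The plan assumes that the effect size "at the end of the study will be at least 0.40", with two-sided alpha 0.05, power 0.80 and 30% attrition.

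The plan's figure first: a two-sample t-test needs 99.08, so 100 per arm; 100 / 0.70 = 142.9, so 143 per arm, as stated. Conversely, 143 × 0.70 = 100 assessed per arm.

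The remaining inputs are assumptions and are not in the article: a net excess of 5 to 15 messaged controls per 100, 20 to 40% of whom act on the message, each gaining 0.40 SD.

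- Dilution = excess share × share acting × gain.
- Low: 0.05 × 0.20 × 0.40 = 0.004 SD, so d = 0.396.
- High: 0.15 × 0.40 × 0.40 = 0.024 SD, so d = 0.376.
- Power at 100 per arm: 0.804 at d = 0.400, 0.796 at d = 0.396, 0.754 at d = 0.376.
- Extra first general practitioner contacts per 100 controls: 100 × 0.05 × 0.20 = 1 to 100 × 0.15 × 0.40 = 6.

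A message sent after an assessment cannot change that assessment. T1 scores are untouched, messages at T1 or T2 can affect only later scores, and a message at T3 affects no trial outcome.

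**The case against.** The strongest objection is that this argues from silence in a condensed article. The severity advice is not stated to be baseline-only, the full protocol approved by the ethics committee is not shown, and follow-up safety handling is an operational detail that an article may leave out. This stands in part. It limits confidence and is why the fix is conditional. It does not remove the point, because the empty WSQ cells are a positive statement, and following the article as written leaves a later high score without the advice that the plan itself motivates.

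The mitigating facts also stand: suicidal intent leads to exclusion at entry, women already above the cut-offs have been advised, and both arms may use usual care throughout. None of these tells a woman that her score has newly crossed a cut-off.

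Two stronger readings are tempting, and the documents support neither.

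- A reader might count the weeks from a high T1 or T2 score to the T3 WSQ and call that the delay in advice. The WSQ item measures suicidality. A woman with a high CES-D score and no suicidality triggers nothing at T3 either, so no such delay can be computed.
- A reader might infer that the trial has no safety procedure at all during follow-up. The article shows only that it describes none tied to a T1 or T2 score.

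**Conclusion.** The point holds as a description of the published plan. No severity score triggers advice at T1, T2 or T3, and the suicidality call cannot operate at T1 or T2. The first part assumes that the severity advice is an entry step; the second follows directly from Table 1. The gap is the same in both arms and is confined to women who first cross a cut-off after entry, in unknown number.

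It is a safety matter that should be put right. It is no error in the sample size, which reproduces, and no threat to the validity of the analysis. Confidence is medium, because the full protocol may already cover follow-up.

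**What to change.** Send the existing advice message automatically, in both arms, after any submitted T1, T2 or T3 assessment with CES-D ≥ 25 or HADS-A ≥ 12. Log each trigger and report the numbers by arm and visit. If the full protocol already repeats the advice at follow-up, a sentence saying so is enough and conduct need not change.

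The cost is an automatic message from the existing online questionnaire and a short amendment. The downside is a little more usual care, possibly more among controls. This may slightly dilute the contrast at T2 and T3 (by 0.004 to 0.024 SD under the assumed inputs, with power between 0.80 and 0.75) and add some general practitioner contacts to the cost comparison. The T1 contrast is unaffected.

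Those contacts should stay in the costs. Removing the first general practitioner visit after a message would not be sound: the TiC-P records care whatever its reason, so a visit caused by the message cannot be told from one that would have happened anyway. The deletion would also depend on a post-randomisation event that may differ by arm.

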### Randomisation

Participants will be randomized in a 1:1 ratio. An independent researcher will create a computer generated randomisation scheme, using blocks of 10. This independent researcher will store the randomisation scheme and provide the next randomisation outcome after each inclusion by the researcher. This procedure ensures blind allocation. All participants will then be informed by e-mail on the randomisation outcome.

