### Intervention

We adapted the existing, evidence based internet version of PST, for use in pregnant women
[25]. We added psychoeducation on pregnancy and affective symptoms and adjusted the example patients in the programs. We named the intervention ‘MamaKits online’. The core assumption of PST is that affective symptoms are generated when people become overwhelmed by practical problems they face in their daily lives. When people are able to make a list of their worries and problems, and learn structured ways to resolve them, they feel less overwhelmed. Then they are better able to cope and this will in turn alleviate their mood
[19].

The course takes 6 weeks to complete, with one lesson each week. Each lesson consists of: information, examples and homework assignments. The intervention consists of three steps: (1) participants describe what really matters to them (2) participants write down their current worries and problems and categorize them into three types: (a) unimportant problems (problems unrelated to the things that matter to them), (b) problems which can be solved, and (c) problems which cannot be solved (e.g. the loss of a loved one), (3) participants make a plan for the future in which they describe how they will try to accomplish those things that matter most to them.

The core of the intervention consists of a structured approach to solve potentially solvable problems. It consists of six steps: (1) write a clear definition of the problem, (2) generate multiple solutions to the problem, (3) select the best solution, (4) work out a systematic plan for this solution, (5) carry out the solution, and (6) evaluate as to whether the solution has resolved the problem.

Trained coaches will give weekly feedback on the assignments through e-mail. The coaches will be master level psychology students, psychologists and psychiatrists who will receive a three hour training by an experienced PST therapist and are afterwards closely supervised by the same person. Based on previous experience with e-mail coaching we expect the coaching to take 15–30 minutes per participant per lesson. Feedback is aimed at supporting participants to work through the intervention and assignments, not to develop a therapeutic relationship. The main researcher, an experienced psychiatrist (HH), will check the integrity of the feedback.

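### A fixed block of 10 leaves about one allocation in six knowable in advance to anyone who knows the block size and past outcomes, so the claim that the procedure ensures blind allocation is too strong

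*Protocol article*

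**What the plan says.** All of the allocation procedure stands in the Randomisation section of the protocol article.

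- Ratio: "Participants will be randomized in a 1:1 ratio".
- Scheme: "An independent researcher will create a computer generated randomisation scheme, using blocks of 10". One scheme is described, with no strata and no variation in block size.
- Release: "This independent researcher will store the randomisation scheme and provide the next randomisation outcome after each inclusion by the researcher".
- Claim: "This procedure ensures blind allocation".
- After allocation: "All participants will then be informed by e-mail on the randomisation outcome".

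The arms cannot be masked. Under Study design: "The study is a randomized controlled trial with an active intervention arm and a waiting list control condition". Under Intervention, the main researcher "will check the integrity of the feedback" that coaches give, and only women in the intervention arm receive that feedback during the trial.

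The section does not say who receives each released outcome, or whether the person who includes women knows the block size.

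**The concern.** Concealment needs two things: the list must be out of reach, and the next entry must not be deducible from earlier ones. Independent custody and release after inclusion give the first. A constant block size works against the second. In an open trial, once five women in a block have gone to one arm, the rest of that block is known to anyone who has kept count.

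If someone who can influence entry knows the next arm, that person could affect who enters it, for example through the order or timing in which ready inclusions are processed. Comparability at baseline would then no longer rest on chance alone. The article states the block size and makes an absolute claim about what the scheme achieves, so this is not a detail left to a fuller document.

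**Working it through.** **Inputs.** Ratio 1:1 and block size 10 (Randomisation), hence five places per arm in each block. Planned total 286 (Abstract), or 143 per arm (Sample size and statistical analysis).

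**The plan's own figure.** The article gives no figure for predictability. Its sample size does reproduce: d = 0.40, two-sided alpha 0.05 and power 0.80 give 99.08 per arm by the t-test, rounded up to 100. Then 100/0.70 = 142.9, so 143 per arm. Nothing below affects this.

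**Certain allocations in a full block.** There are C(10,5) = 252 equally likely blocks. A place is certain when one arm's quota is already used up, so the number of certain places is the length of the run of identical assignments at the end of the block. The number of blocks with a final run of exactly j is 2 × C(9 − j, 4):

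| Final run j | Blocks | Share |
|---|---|---|
| 1 | 140 | 55.6% |
| 2 | 70 | 27.8% |
| 3 | 30 | 11.9% |
| 4 | 10 | 4.0% |
| 5 | 2 | 0.8% |

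Mean = (140 + 140 + 90 + 40 + 10)/252 = 420/252 = 1.667 per block, or one in six. The general form for a block of 2m is 2m/(m + 1), here 10/6. The last place is always certain, and at least two places are certain in 44.4% of blocks.

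**Whole trial.** 286 is 28 full blocks plus 6 places. In the partial block only the sixth place can be certain, with probability 2/252 = 0.008. Total: 28 × 1.667 + 0.008 = 46.7, and 46.7/286 = 16.3%.

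**Best guess.** Guessing the arm with more places left, and tossing a coin when they are equal, is right for 6.53 of 10 allocations in a full block (65.3%), against 50% with no information.

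**Alternatives.** For varying sizes, 286 allocations were simulated with the sizes drawn with equal probability. The observer knows the possible sizes and every past outcome, but not the size of the current block.

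| Scheme | Certain | Best guess right |
|---|---|---|
| Fixed 10 | 16.3% | 65% |
| Fixed 6 | 25% | 68.3% |
| Fixed 4 | 33% | 70.8% |
| Random 4, 6, 8 | about 2% | about 68% |
| Random 6, 8, 10 | about 1.5% | about 66% |
| Random 8, 10, 12 | about 1.2% | about 65% |

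The guess rates for mixed sizes agree with the size-weighted average of the fixed-block values. For 4, 6 and 8: (2.833 + 4.100 + 5.329)/18 = 68.1%. For 8, 10 and 12: (5.329 + 6.532 + 7.716)/30 = 65.3%.

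**The case against.** **The figures assume knowledge that the article does not attribute to anyone.** The text says only that the independent researcher will "provide the next randomisation outcome after each inclusion by the researcher". It does not name the recipient, or say that one person handles all inclusions or knows the block size. The main researcher who checks feedback need not be the person who includes women. A reader might infer that the including researcher learns every allocation; the article does not state that. This part of the objection stands, so the 16.3% is conditional. It does not rescue the absolute claim, because nothing in the described procedure prevents such knowledge.

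**There is little room to act on a prediction.** Under Recruitment, women register online, and all who register receive the information, the consent form and the questionnaire link. Signed consent and a completed baseline questionnaire come before randomisation. Under Inclusion and exclusion criteria, entry depends on age, due date, self-report cut-offs and one suicidality item. Severe symptoms and concurrent treatment do not exclude. A reader might suppose that the researcher can choose which incomplete consents or questionnaires to pursue, but no such step is described. This stands and keeps the practical risk modest. What remains is the order and timing of processing, on which the article is silent.

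**Ten is already a fairly large block.** This is true: a smaller fixed block would be worse, as the table shows. It also means that varied sizes are a poor remedy if they are too small. Sizes 4, 6 and 8 would remove most certain allocations but raise the best-guess rate from 65% to about 68%.

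**Conclusion.** The point holds in a conditional form. The procedure conceals the list, but it does not by itself ensure that the next allocation is unknown. To anyone who knows the block size and the past outcomes, about 47 of 286 allocations (16.3%) are certain.

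This rests on three assumptions: a single list, which is the natural reading of the section; a constant size of 10, which is stated; and an observer who has both pieces of information, which the article neither states nor rules out. If the including researcher were kept from past outcomes, the figure would not apply.

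A reader might go further and conclude that the trial suffers from selection bias. The article does not support that: predictability is an opportunity, and the described entry route leaves little scope to use it. The self-reported, unmasked outcomes are a separate matter and do not change how predictable the list is. The weight is modest, but the correction is specific and nearly free.

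**What to change.** In the Randomisation section, replace the fixed block by permuted blocks whose size varies at random and is not smaller on average, for example 8, 10 and 12. The independent researcher should generate and hold the list, and the sizes should not be disclosed to the including researcher or the coaches. Even an observer who knows the set of possible sizes would then be certain of about 1.2% of allocations, roughly 3 or 4 of 286, with the best-guess rate unchanged at about 65%.

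The cost is a setting in the program that generates the list. The one statistical downside is a slightly larger possible difference in arm sizes if recruitment stops within a block: at most 6 instead of 5. The sample size does not change.

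If randomisation has already begun, leave the list alone. Limit the claim to concealment of the list by independent custody and release after inclusion, and state who knew the block size and the past outcomes during recruitment.
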